## Abstract

**Introduction:**

Chronic kidney disease (CKD) affects up to 16% of adults in the UK. Patient quality of life is particularly reduced in end-stage renal disease and is strongly associated with increased hospitalisation and mortality. Thus, accurate and responsive healthcare is a key priority. Electronic patient-reported outcome measures (ePROMs) are online questionnaires which ask patients to self-rate their health status. Evidence in oncology suggests that the use of ePROM data within routine care, alongside clinical information, may enhance symptom management and improve patient outcomes. However, National Health Service (NHS)-based ePROM research in CKD is lacking. This pilot trial will assess the feasibility of undertaking a full-scale randomised controlled trial (RCT) in patients with CKD within the NHS.

**Methods and analysis:**

The renal ePROM pilot trial is an investigator-led single-centre, open-label, two-arm randomised controlled pilot trial of 66 participants ≥18 years with advanced CKD. Participants will be randomised to receive either usual care or usual care supplemented with an ePROM intervention. Participants within the intervention arm will be asked to submit monthly self-reports of their health status using the ePROM system. The system will provide tailored information to patients in response to each report and notify the clinical team of patient deterioration. The renal clinical team will monitor for ePROM notifications and will respond with appropriate action, in line with standard clinical practice. Measures of study feasibility, participant quality of life and CKD severity will be completed at 3 monthly intervals. Health economic outcomes will be assessed. Clinicians will record treatment decision-making. Acceptability and feasibility of the protocol will be assessed alongside outcome measure and intervention compliance rates. Qualitative process evaluation will be conducted.

**Ethics and dissemination:**

The findings will inform the design of a full-scale RCT and the results will be submitted for publication in peer-reviewed journals. The study has ethical approval.

**Trial registration numbers:**

ISRCTN12669006; Pre-results.

Strengths and limitations of this studyThe study uses a randomised controlled trial (RCT) design, delivered in a National Health Service (NHS) setting.The research site, University Hospitals Birmingham NHS Foundation Trust, hosts one of the largest specialist renal research sites in Europe.The study protocol and intervention was developed by a multidisciplinary team of experts including: patients, healthcare professionals and academics.As a pilot trial, the study is limited to one clinical centre and is not statistically powered to assess clinical outcomes. Instead, the project will evaluate feasibility of conducting a full-scale RCT in the target population.

## Introduction

Chronic kidney disease (CKD) affects up to 16% of adults in the UK,^1^ with an annual estimated cost of £1.45 billion.^2^ More than half of these costs were associated with renal replacement therapy (RRT)—haemodialysis, peritoneal dialysis and/or kidney transplantation—for patients with end-stage renal disease (ESRD).^2^ This is despite the fact that patients requiring RRT comprise less than 1% of the total CKD population.^2^ Numerous studies have demonstrated that patients with ESRD experience high symptom burden and a very high prevalence of depression.^3^ Moreover, patient quality of life is significantly reduced in ESRD and is strongly associated with increased hospitalisation and mortality.^3^ Accurate and responsive healthcare for patients as they progress from advanced CKD to ESRD is therefore a key healthcare priority.

Effective management of advanced CKD relies on the timely detection of clinical deterioration towards ESRD. This can be a major challenge between scheduled clinic visits, when it is often difficult to identify clinical deterioration unless a patient self-refers. Unfortunately, some patients self-refer too late because they have difficulty identifying the point at which they may require assistance. Without prompt recognition of advanced symptoms, such patients are at high risk of severe illness, emergency hospitalisation and associated worse clinical outcomes.^3^

Patient-reported outcome measures (PROMs) are validated questionnaires which ask patients to self-rate their health status. They can provide important information regarding the patient’s perspective on the physical, functional and psychological consequences of treatment and the degree and impact of disease symptoms.^4^ Evidence suggests that the use of PROM data, alongside regular clinical information, within routine care may:Aid patient–provider communication and support shared decision-making.^5^Improve patient activation and help patients to feel more involved/empowered in decisions around their care.^6–8^Improve the accuracy of symptom assessment and enhance symptom management.^9^Enhance patient education and self-management and maximise patient safety.^7 10–15^

With recent advances in technology, there has been considerable interest in the use of electronic PROMs (ePROMs) for the routine monitoring of patients with long-term conditions. ePROMs offer patients an ‘electronic’ method of data entry—for example, web based via PC, smartphone or using tablet devices—and give clinicians a flexible platform with which they may view PROM data.^14 16 17^

ePROMs offer patients the option of inputting data at a time and place, and via a platform, that is convenient to them. ePROM data can be used to help provide patients with tailored advice on self-management and can provide clinicians with detailed health-related quality of life (HRQL) and symptom data both in clinic and between scheduled appointments via home/remote data capture.^15^

For patients with advanced CKD, this would allow clinicians to monitor for symptom deterioration, facilitating the early detection of problems requiring attention and promoting timely intervention from the clinical team (eg, advice aimed at aiding patient self-management or escalation of care). Such intervention may delay disease progression and the need for costly and invasive RRT, and reduce emergency hospitalisations and other adverse outcomes.

A recent randomised controlled trial (RCT) conducted in an oncology setting in the USA, demonstrated that ePROM use is associated with improved HRQL, reduced accident and emergency visits, reduced hospitalisations and superior quality-adjusted survival.^15^ Both in Canada and Denmark, ePROM collection has been shown to be feasible in a renal population.^16 18 19^ However, National Health Service (NHS)-based ePROM research in CKD, utilising real-time patient and clinician feedback is lacking. Routine remote use of ePROM data by patients with advanced CKD may aid self-management, while also helping to improve the flow of information between patients and their clinicians, potentially improving patient safety, enhancing clinical interactions, optimising patient outcomes and delivering cost savings to the NHS.

A RCT is needed to evaluate ePROM efficacy in advanced CKD to determine if health professionals, providers and policy-makers should implement routine ePROM collection in renal practice. However, before a definitive trial is undertaken, a pilot trial is required to assess the feasibility of undertaking such a study and to help inform the key elements (eg, appropriate outcome measure, sample size) of the design for the full-scale RCT.

## Methods

### Design

The renal ePROM (RePROM) study will span two phases: stage 1 involves development of the ePROM intervention with patient and clinician input; stage 2 is a pilot/feasibility RCT with a qualitative substudy.

### Setting

Patients under the care of the renal services at Queen Elizabeth Hospital Birmingham (QEHB) will be recruited for this study.

#### Stage 1: intervention development

Design of the ePROM system will be finalised during a series of operational meetings, held in stage 1 of the study, with regular input from: (1) the QEHB renal clinical and research team; (2) the RePROM patient advisory group (PAG); (3) the QEHB IT and Informatics group; (4) the University of Birmingham Clinical Trials Unit (BCTU) and (5) the Patient CentredOutcomes Group at the University of Leeds.

The ePROM system will be made available to study participants via ‘myHealth@QEHB’, a secure patient portal linked to the patient’s electronic healthcare record (EHR), delivered by the host site. The system will be developed to allow patients to self-report their health status using a variety of electronic platforms, for example, PC, smartphone or tablet.

The ePROM system will be designed to: (1) provide appropriate self-management advice to participants whose questionnaire scores suggest mild/moderate symptoms and (2) notify the clinical team of patient deterioration via an automated email, where the patient’s questionnaire responses indicate severe symptoms/cause for concern.

Patients’ longitudinal ePROM scores will be made available to clinicians for use during routine outpatient consultations via the EHR. The RePROM PAG felt this approach would help to focus clinical discussion on patient-centred issues and may enhance symptom management, a view supported by related literature.^7 8 16 17 20–22^

#### Stage 2: pilot/feasibility RCT and qualitative substudy

##### Trial design

The RePROM pilot trial is an investigator led single-centre, open-label, two-arm randomised controlled pilot trial of 66 participants aged 18 years or over with advanced CKD. Participants will be randomised to receive either usual care or usual care supplemented with an ePROM intervention. The study flow is outlined in figure 1.

**Figure 1 F1:**
[figure not shown]
RePROM trial schema. CKD, chronic kidney disease; QEHB, Queen Elizabeth Hospital Birmingham.

### Recruitment and eligibility

Recruitment is scheduled to commence in July 2018. Patients will be invited to participate based on the following eligibility criteria:

#### Inclusion criteria

Aged ≥18 years old.Ability to provide fully informed written consent for participation in the study.Patients under the care of the renal services at QEHB.Patients meeting the trial definition of advanced CKD:An estimated Glomerular filtration rate (eGFR) ≥6 and ≤15 mL/min/1.73 m^2^ (inclusive).**OR**A projected risk of progression to end-stage renal failure within 2 years ≥20% using the 4-variable Tangri renal risk calculator.^23^

#### Exclusion criteria

Patients unwilling to use the ePROM intervention.Patients who, in the opinion of the consenting professional, cannot speak, read or write English sufficiently well to complete the ePROM unaided.An episode of acute kidney injury (defined in accordance with national guidelines) within the last 3 months.^24^Patients meeting the trial definition of ESRD:Currently receiving dialysis or scheduled to start in the next 2 weeks.Has received (or has a scheduled date to receive) a kidney transplant.eGFR ≤5 mL/min/1.73 m^2^.A terminal illness that, in the opinion of the consultant assessing eligibility, is likely to lead to the death of the patient within 6 months of starting participation in the study.

Patients fulfilling the entry criteria will have their eligibility assessed by qualified personnel at the host research site with access to/full understanding of their medical history. All patients approached will be given a copy of the participant information sheet (PIS). Usually, this will be sent to the patient in the post, along with an invitation letter, normally in advance of their next clinic assessment. The renal research team may also contact the patient by phone at the time of sending out the PIS. Staff will allow time for potential participants to consider the information provided, discuss the trial with their family and friends, and decide whether to take part. Alternatively, if deemed appropriate by the recruiting renal research team member, the PIS and invitation letter may be provided directly in clinic. Provided the patient feels they have had sufficient time to consider their potential involvement, consent may be sought at this same appointment.

Investigators/delegate(s) will ensure that they adequately explain the aim, trial intervention, anticipated benefits and potential hazards of taking part in the trial to the participant. They will also stress that participation is voluntary and that the participant is free to refuse to take part and may withdraw from the trial at any time. The participant will be given the opportunity to ask questions. If the participant expresses an interest in participating in the trial, they will be asked to sign and date the latest version of the informed consent form (ICF).

### Trial intervention

Participants in the control arm will continue to receive usual care. Participants randomised to the intervention arm will be asked to commence monthly self-reporting of their health status using the ePROM system, after receiving a face-to-face training session.

Participants will receive automated reminders prior to each scheduled self-report and 24 hours after a failure to report if necessary, these will be delivered via a secure myHealth QEHB patient portal email or text message, according to participants’ preferences. Participants may also upload additional ad hoc reports to the system, if they feel this is necessary (eg, if they wish to communicate a sudden change in symptoms).

The ePROM system will provide tailored information to patients in response to each report (both scheduled and ad hoc) and alert the clinical team of patient deterioration according to a priori determined alert threshold criteria established in the intervention development stage. After receiving training during the study setup period, the renal clinical team will monitor for ePROM alerts and will respond with appropriate clinical action, in line with standard clinical practice.

### Randomisation

Participants will be randomised at the level of the individual in a 1:1 ratio to either usual care (control arm) or usual care supplemented with an ePROM) system (experimental arm). A minimisation algorithm will be used within the online randomisation system to ensure balance in the treatment allocation over the following variables:Risk progression (<40%, vs ≥40%, using the 4-variable Tangri renal risk calculator^23^).Self-reported computer experience (defined as: regular use of a computer or tablet or smartphone at least weekly vs less than weekly).Ethnicity (‘white’ vs ‘non-white’).

A ‘random element’ will be included in the minimisation algorithm, so that each patient has a probability (unspecified here), of being randomised to the opposite treatment that they would have otherwise received.

### Outcome measures and study procedures

#### Primary outcome

The primary aims of the study are to pilot the trial protocol and assess the feasibility of undertaking a full-scale RCT on the use of ePROMs in the management of advanced CKD. This will include assessment of both quantitative and qualitative data. The pilot study will:Test and pilot the trial protocol (including recruitment and retention rates, data collection processes, data completeness and adherence to the ePROM intervention).Assess the willingness of clinicians to randomise participants into the trial.Assess the willingness of people with advanced CKD to be randomised into the trial.Assess the acceptability of the ePROM intervention;Explore the need for a non-web-based intervention platform for participants who are unable to use the ePROM.Inform selection of the most appropriate primary outcome measure for the full-scale RCT.Provide data to help estimate the sample size for the full-scale RCT.Provide a platform to develop and pilot the processes to capture costs and outcomes to inform the health economic evaluation for the full-scale RCT.Determine key participation criteria for centre involvement in the full-scale RCT.

#### Outcome data

This pilot trial is not powered to detect differences in outcome measures, but it provides the opportunity to ensure that there are no issues with completion of the outcome data and proposed outcome measures for the main RCT. The following outcome data will be collected:HRQL data, using the paper version of the EuroQol five dimension, five level, questionnaire (EQ-5D-5L). The EQ-5D-5L is a reliable/validated generic measure of health status/utility commonly used internationally in cost-effectiveness research.^25^Clinical data including: serum creatinine, calcium, phosphate, bicarbonate, albumin, eGFR, Albumin-to-creatinine ratio (ACR), blood pressure and for participants with diabetes: glucose and glycosylated haemoglobin (HbA1c).The following event data: progression to ESRD, contact with healthcare professionals in secondary care (outpatient clinics and accident and emergency), inpatient hospitalisation, death.Healthcare resource use data will be collected at each study visit.

All study staff/participants will be invited to complete a trial process questionnaire at the end of the study, which will evaluate aspects surrounding: data collection forms/questionnaires; randomisation procedure; acceptability of the intervention; appropriateness of the frequency of ePROM reporting; alert thresholds and management.

### Study procedures

During the baseline visit, patients will have demographic details recorded including age, self-assigned ethnicity, educational status, residential postcode (to derive Index of Multiple Deprivation), self-reported computer experience and medical history.

Patient quality of life will be assessed using a paper version of the EQ-5D-5L questionnaire (not a routine test). This will be completed by the participant at baseline and at 3, 6, 9 and 12 months postrandomisation (assessment window ±3 weeks). This questionnaire may be posted out to participants prior to their scheduled clinic/research visit, but research staff will be on hand in clinic to assist with completion where required. The EQ-5D-5L instrument is a reliable/validated generic measure of health status commonly used in CKD trials research.^25^

Clinical data will be collected at baseline and at 3, 6, 9 and 12 months (assessment window ±3 weeks), including: serum creatinine, calcium, phosphate, bicarbonate, albumin, eGFR, ACR, blood pressure and for participants with diabetes: glucose and HbA1c. Since these measures are routinely collected for clinical monitoring, the results closest to the calculated visit due date will be used for trial data, rather than repeating tests which have already been performed. If a result is not available within the visit window, the test should be performed at the trial visit. Healthcare resource use will be collected at 3, 6, 9 and 12 months (assessment window ±3 weeks).

All data will be extracted from the source records and entered onto a secure database maintained by the BCTU after each scheduled follow-up visit. The database will automatically capture ePROM notification data. Between clinic visits, patients will be managed in accordance with local practice.

### Sample size and justification

As this is a pilot trial, no formal sample size calculation has been performed. Following recommendations for pilot studies, 30 patients or more are typically required to obtain estimates of the parameters needed for sample size estimation.^26 27^ To allow for a 10% drop-out and loss to follow-up rate, this pilot trial will aim to recruit at least 33 participants in each group, a total of 66 participants. This will also allow the recruitment and retention rates to be estimated with 95% CI maximum widths of 20% and 25%, respectively.

### Analysis of outcome measures

A separate Statistical Analysis Plan will be produced and will provide a more comprehensive description of the planned statistical analyses. A brief outline of these analyses is given below.

The primary comparison groups will be composed of those randomised to usual care (control group) versus those randomised to usual care supplemented with the ePROM intervention (experimental group). In the first instance, all analyses will be based on the intention to treat principle, that is, all participants will be analysed in the treatment group to which they were randomised irrespective of compliance with the allocated treatment or other protocol deviation. The data analysis for this pilot trial will be descriptive and mainly focus on CI estimation, with no hypothesis testing performed.

Data will be explored to assess the key feasibility aspects of undertaking a full-scale RCT on the use of ePROMs in the management of advanced CKD. Dichotomous feasibility measures, such as the recruitment and retention rates, as well as data completeness, will be reported as numbers and percentages. Where appropriate, these values will be summarised across treatment groups.

Adherence with the ePROM intervention will be assessed by calculating the number and percentage of participants who complete the ePROM reports as scheduled. To be considered adherent, participants will need to have submitted their report within 72 hours of the scheduled time point. Incomplete submissions (ie, with some questions not answered) will be accepted for the purpose of measuring adherence. Ad hoc ePROM reports (ie, those completed outside the scheduled reporting periods) will not contribute to the assessment of adherence, although we will assess the number of ePROM reports completed by each participant.

The pilot data will also help inform the selection of the most appropriate primary outcome measure for the main RCT and provide data to facilitate estimation of the sample size required for the main RCT. Outcome data on HRQL and clinical data are collected at 3, 6, 9 and 12 months postrandomisation. Analysis methods will be chosen according to the data type of the outcome under investigation, in brief:Continuous endpoints (eg, quality of life): These data will be summarised using means and SDs, with differences in means with 95% CIs reported. Longitudinal plots of the data over time will also be constructed for visual presentation of the data.Categorical (dichotomous) endpoints (eg, hospitalisation rates): The number of participants and percentages experiencing the event will be summarised between groups.Time-to-event endpoints (eg, time to ESRD, mortality): The numbers of participants and percentages experiencing the event will be summarised over time between groups. Kaplan-Meier survival curves will be constructed for visual presentation of time-to-event data.

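### Kaplan-Meier for time to ESRD, drawn conventionally, would modestly overstate absolute ESRD risk if deaths precede ESRD; a cumulative incidence curve is a free improvement

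*Protocol article*

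**What the plan says.** Under Analysis of outcome measures, the protocol article groups its endpoints by data type. One group reads "Time-to-event endpoints (eg, time to ESRD, mortality", so ESRD and death are named separately and no composite is mentioned. Two outputs are planned for this group. The first is tabular: "The numbers of participants and percentages experiencing the event will be summarised over time between groups". The second is graphical: "Kaplan-Meier survival curves will be constructed for visual presentation of time-to-event data".

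Both events are collected. The Outcome data section lists "The following event data: progression to ESRD, contact with healthcare professionals in secondary care (outpatient clinics and accident and emergency), inpatient hospitalisation, death".

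The same analysis section limits the purpose: "The data analysis for this pilot trial will be descriptive and mainly focus on CI estimation, with no hypothesis testing performed". It also says that "The pilot data will also help inform the selection of the most appropriate primary outcome measure for the main RCT" and that the data will help to estimate the main trial's sample size. It presents itself as an outline: "A separate Statistical Analysis Plan will be produced and will provide a more comprehensive description of the planned statistical analyses".

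The article gives no rule for a participant who dies before ESRD, no expected mortality and no expected ESRD rate.

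**The concern.** Kaplan-Meier suits mortality, because nothing prevents death from being observed later except the end of follow-up or loss. ESRD is different: a participant who dies first can no longer reach it. The usual Kaplan-Meier calculation for ESRD alone censors that participant at death, and so treats them as someone who might still have progressed. One minus the curve then estimates ESRD risk in a setting without death, which is higher than the share of participants who will reach ESRD.

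The pilot is meant to supply planning values for a full trial. If ESRD becomes a candidate outcome and the 12-month value is read off this curve, the expected number of events will be somewhat too high.

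**Working it through.** **The plan's own figures.** The Sample size section aims for 33 per group: "this pilot trial will aim to recruit at least 33 participants in each group, a total of 66 participants". Taking the base of 30 as per group (inferred), 30 × 1.10 = 33. Dividing by 0.90 gives 33.3, or 34, a difference of one that does not matter here. No ESRD or mortality figure is stated, so there is none to reproduce.

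**Inputs.**
- Participants per arm: 33 (Sample size and justification).
- Follow-up: 12 months (Planned final analyses).
- 2-year ESRD risk: 20%, 40% and 60%. The 20% is the floor of one of two alternative entry criteria, the 40% is the minimisation cut-point, and the 60% is assumed. Using any of them as the cohort's risk is an assumption.
- 12-month mortality: 2%, 5%, 10% and 15%, all assumed.

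**Formulas**, with constant cause-specific hazards per year:
- ESRD hazard h = −ln(1 − 2-year risk) / 2
- Death hazard m = −ln(1 − 12-month mortality)
- One minus Kaplan-Meier at 12 months = 1 − exp(−h)
- Cumulative incidence with death competing = h/(h + m) × [1 − exp(−(h + m))]

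**Worked case: 2-year risk 40%, mortality 10%.**
- h = 0.2554 and m = 0.1054, so h + m = 0.3608.
- One minus Kaplan-Meier = 1 − exp(−0.2554) = 22.5%.
- Cumulative incidence = 0.2554/0.3608 × (1 − 0.6971) = 0.708 × 0.303 = 21.4%.
- The gap is 1.1 points, and 33 × 0.011 = 0.36 of a participant per arm.

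**Full grid at 12 months.** The last column is 1.96 × √[p(1 − p)/33], with p equal to one minus Kaplan-Meier.

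| 2-year ESRD risk | 1 − KM | Cumulative incidence at mortality 2 / 5 / 10 / 15% | Gap (points) | 95% CI half-width, n = 33 (points) |
|---|---|---|---|---|
| 20% | 10.6% | 10.5 / 10.3 / 10.0 / 9.8% | 0.10 to 0.80 | 10.5 |
| 40% | 22.5% | 22.3 / 22.0 / 21.4 / 20.9% | 0.22 to 1.66 | 14.3 |
| 60% | 36.8% | 36.4 / 35.9 / 35.0 / 34.1% | 0.34 to 2.62 | 16.5 |

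The gap is about 1% to 8% in relative terms. The largest is 33 × 0.0262 = 0.87 of a participant per arm, and 2.62/16.5 is about one sixth of the CI half-width. A stress case outside the grid (12-month ESRD risk 50%, mortality 20%) gives 50.0% against 45.4%, a gap of 4.6 points against a half-width of 17.1.

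**The tabulated percentages.** With complete follow-up, the number reaching ESRD divided by the number randomised keeps deaths in the denominator and equals the cumulative incidence. With losses it does not. Take the worked case, add a constant loss hazard c = −ln(0.90) = 0.1054 for the 10% allowed, and assume that lost participants stay in the denominator as non-events. The total hazard is 0.2554 + 0.1054 + 0.1054 = 0.4661. The observed percentage is 0.2554/0.4661 × [1 − exp(−0.4661)] = 0.548 × 0.373 = 20.4%. The table would then show 20.4% and the curve 22.5%, on either side of 21.4%.

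**The case against.** The strongest reply is that the article states no censoring rule, calls itself an outline and leaves detail to a separate SAP that is not shown. That stands in part. Censoring at death is inferred from how the method is ordinarily applied, and the SAP may already deal with it. But the method itself is stated, for an endpoint named apart from mortality. Counting deaths as events would turn the curve into ESRD or death, which is not the endpoint named. The point therefore concerns a stated choice, not a missing detail.

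A second reply is that the curves are only for display in a descriptive pilot without tests, beside percentages that are free of this bias. The first half stands and keeps the matter minor. The second half holds only with complete follow-up.

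Two stronger readings are tempting and are not supported:
- **That mortality in this population is appreciable.** The article gives no mortality rate, and it excludes patients with a terminal illness likely to be fatal within 6 months. The point must be put conditionally: if deaths occur before ESRD.
- **That unequal deaths between arms would distort the displayed ESRD contrast.** Under the constant, independent hazards used above, one minus Kaplan-Meier is 1 − exp(−h) and depends only on the ESRD hazard. Arms with equal ESRD hazards would show the same expected curve however their deaths differed, and it is the cumulative incidence curves that would separate. The two displays answer different questions. The case for change rests on absolute risk, not on the contrast.

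**Conclusion.** The point holds as a minor one. A conventional Kaplan-Meier curve for ESRD alone overstates the 12-month absolute risk whenever deaths precede ESRD, by about 0.1 to 2.6 percentage points over the grid used. This would not alter a feasibility conclusion.

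The direction follows from the method, provided that deaths are censored. The size depends on the assumed mortality, the assumed ESRD risks and constant hazards. Sampling error swamps the bias in the pilot, but a larger main trial does not remove a bias carried into its planning rate. That is the only route by which it could matter, and the article does not say that ESRD will be the main trial's outcome.

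**What to change.** In the SAP, replace the Kaplan-Meier curve for time to ESRD with the Aalen-Johansen cumulative incidence by arm, with death as a competing event and a 95% CI at 12 months. Use that figure if an ESRD rate is carried into planning of the main RCT. It accounts for death and, if censoring is non-informative, for loss to follow-up, which neither planned output does alone. Keep Kaplan-Meier for all-cause mortality and, if wanted, add it for ESRD or death.

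The cost is about one sentence in the SAP and standard software. ESRD and death are already collected, so no new data are needed, and the sample size and visit schedule do not change.
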